### Outcome Measures

The primary outcome of this study will be the uptake of PPSV-23 in each arm, assessed 1 month after the intervention using administrative records. The secondary outcomes will include: (1) vaccine confidence, measured by 4 survey statements related to perceptions of the importance, safety, and efficacy of vaccination, as well as vaccine management; (2) influenza vaccination, defined as participants receiving the influenza vaccine after enrollment in the study, verified through administrative records, with the cost of the vaccination borne by the participants; (3) cost per person vaccinated and cost-effectiveness; (4) vaccine knowledge between the 2 groups; (5) attitudes toward vaccination; (6) willingness to vaccinate; (7) gratitude, measured by the GQ-6 scale; (8) the rate of successful vaccine referral, defined as participants successfully recommending PPSV-23 to others in the community after participating in the study; and (9) incidence of adverse events or reactions to vaccination.

### Statistical Analysis

#### Primary Outcome

Descriptive analysis will be used to summarize the sociodemographic characteristics, knowledge, attitudes, and behaviors of the participants in each arm. Cronbach α will be used to test the reliability of the scales in the questionnaire. For the primary analysis, we will conduct intention-to-treat and per-protocol analyses, using logistic regression to compare the odds ratios of vaccination rates between the pay-it-forward group and the standard-of-care group, with adjustment for sociodemographic characteristics (eg, sex, age, and education level). In addition, we will perform logistic regression analyses stratified by income level, chronic disease status, living status, and distance to the vaccination site.

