### Sample Size

The sample size was calculated using the PASS 2021 software after conducting a pilot trial. In the pilot trial, 88% (23/26) of the participants in the pay-it-forward group and 12% (3/26) of the participants in the standard-of-care group received the pneumonia vaccine. On the basis of the pilot trial results, we initially calculated the sample size to be 16. However, this sample size was determined to be too small to detect the desired effect size for the trial. To address this, we reviewed previous data on vaccination rates and estimated the expected difference in rates between the 2 groups based on prior experience. An earlier review indicated that the vaccination coverage of PPSV-23 among older adults in China ranged from approximately 1.23% to 42.10% [16]. Our previous pilot study showed that the pay-it-forward intervention increased influenza vaccination coverage in older adults by approximately 30% [23]. Considering these, we estimated a PPSV-23 vaccination coverage of 10% in older adults, and projected that the pay-it-forward intervention would increase this by 20%. The power of the test was set as 90% using a 2-sided test with a significance level of.05. The minimum sample size was calculated to be 158. After accounting for a 20% dropout rate, the minimum sample size required was adjusted to 198. The minimum sample size was further increased to 204 to accommodate the block-randomized design. Consequently, at least 204 participants were required for the trial.

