#### Secondary Outcomes

The economic evaluation will be conducted from a health care provider’s perspective with a 1-year time horizon. Microcosting methods will be used to evaluate the implementation costs of both the standard-of-care and pay-it-forward intervention groups. Specifically, we will collect cost data, including personnel time, medical supplies, equipment use, and facility expenses. Material procurement costs will be calculated using primary sources, such as invoices, while project implementation costs will be based on researchers’ self-reported data. Health care personnel’s time costs will be estimated using the local government–published wage standards. A decision tree model will be developed using TreeAge Pro 2022 software (TreeAge Software, LLC), with vaccination uptake (defined as the number of vaccinated individuals per intervention arm) serving as the effectiveness measure for the pay-it-forward intervention. The intervention will be compared against standard-of-care (participants’ self-paid PPSV-23 vaccination) to estimate incremental costs and incremental cost-effectiveness ratios. Model robustness will be assessed through 1-way sensitivity analyses and probabilistic sensitivity analysis. Influenza vaccination rates and vaccine confidence will be compared between the pay-it-forward intervention group and the standard-of-care group using logistic regression analyses, adjusted for sociodemographic information. Other secondary outcomes will be summarized using descriptive statistics and compared between the 2 arms.

Participants with missing primary outcome data (ie, vaccination status) will be reviewed. A complete case analysis will be performed if the proportion of missing primary outcome data is low (<5%). If the missing data exceed this threshold, multiple imputation methods will be applied under the assumption that the data are missing at random, to account for potential bias. Sensitivity analyses will also be conducted to assess the robustness of the findings under different assumptions about the missing data. To address missing follow-up data, we will use the last observation carried forward method or a multiple imputation method for missing values for categorical and continuous variables.

The results of all logistic regression analyses will be reported as crude odds ratios and adjusted odds ratios, along with 95% CIs. All statistical tests will be 2-sided, with a significance level of *P*<.05.

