## Results

Participant recruitment took place from January 2024 to September 2024. We enrolled 220 participants. Final results are anticipated in June 2026.

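### Subgroups are planned only as stratified logistic regressions, which do not test whether the effect differs between strata and can give discordant significance by chance

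*Protocol article*

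**What the plan says.** The Statistical Analysis section, under Primary Outcome, sets an adjusted logistic regression as the main comparison, "using logistic regression to compare the odds ratios of vaccination rates between the pay-it-forward group and the standard-of-care group". It then adds one sentence on subgroups: "we will perform logistic regression analyses stratified by income level, chronic disease status, living status, and distance to the vaccination site". No arm-by-factor term is named, the analyses are not described as exploratory, and neither the number of levels nor any cut-point is given for the four factors.

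The end of the Secondary Outcomes subsection covers all analyses. Logistic regression results are to be given as crude and adjusted odds ratios with 95% CIs, and "All statistical tests will be 2-sided, with a significance level of *P*<.05".

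The figures that fix how much information a stratum holds are in the Sample Size and Results sections: "we estimated a PPSV-23 vaccination coverage of 10% in older adults, and projected that the pay-it-forward intervention would increase this by 20" per cent, "at least 204 participants were required for the trial", and "We enrolled 220 participants".

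**The concern.** Whether the intervention works differently in different groups is a question about the difference between stratum effects. A separate regression in each stratum asks only whether the effect in that stratum differs from zero. With each stratum holding a fraction of the participants, some strata can miss significance and others reach it although the true effect is the same in all.

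This matters because income is a policy axis of the trial. Study Design and Setting selects districts of high, middle and low income, and Aims and Hypotheses says that the results should inform decisions on vaccine subsidy. A chance contrast between income strata could be taken for a real difference in who benefits.

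**Working it through.** **Inputs.** From Sample Size: control uptake 10%, intervention uptake 30%, two-sided 0.05, 90% power, 20% dropout, 204 planned. From Results: 220 enrolled. From the Abstract: 1:1 allocation, so about 110 per arm. The pilot rates, also in Sample Size, are 3/26 (12%) and 23/26 (88%). Assumed, because the article gives nothing: two or three equal strata per factor, and the same true effect in each.

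**1. Reproduce the plan's own figure.** With unpooled variance, n per arm = (1.960 + 1.282)² × (0.1×0.9 + 0.3×0.7) / 0.2² = 78.8, so 79 per arm and 158 in total; 158/0.8 = 197.5, so 198. Both match the article, which confirms that the planned increase is 20 percentage points.

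**2. Control events.** 110 × 0.10 = 11.0 overall (10.2 at 204 participants). Per equal stratum: 11/2 = 5.5 or 11/3 = 3.7.

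**3. Power within a stratum.** Exact enumeration of the pooled z test at 10% v 30% gives p = 0.772 with 55 per arm (two strata) and p = 0.593 with 37 per arm (three strata; 110/3 = 36.7, rounded up).

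**4. Chance of discordant significance under an identical true effect.**
- Two strata: 2p(1−p) = 2 × 0.772 × 0.228 = 0.352.
- Three strata: 1 − p³ − (1−p)³ = 1 − 0.208 − 0.067 = 0.724.

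At the planned 204 (51 and 34 per arm) these become 39% and 74%. A separate simulation at 220 using Wald tests of the log odds ratio gives 37% and 74%.

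**5. Dependence on the effect size.** Same calculation, 220 participants:

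| True rates | Two equal strata | Three equal strata |
|---|---|---|
| 10% v 30% (planning) | 35% | 72% |
| 12% v 50% (assumed intermediate) | about 1% | about 11% |
| 12% v 88% (pilot) | about 0% | about 0% |

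**6. Precision of a stratum odds ratio.** The planning odds ratio is (0.3/0.7)/(0.1/0.9) = 3.86. At expected counts, two strata, the SE of the unadjusted log odds ratio is √(1/5.5 + 1/49.5 + 1/16.5 + 1/38.5) = 0.54, so the 95% CI runs from about 1.3 to 11. With three strata the SE is 0.66 and the CI runs from about 1.1 to 14. The adjusted models spread the same few events over further terms.

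**7. What a test of heterogeneity does instead.** In the same simulation, with no true difference between strata, it rejects in about 4% of trials (two strata) or 2.5% (three). Its power is low: with two strata the SE of the log ratio of odds ratios is √2 × 0.537 = 0.76, so the ratio detectable with 80% power is exp((1.960 + 0.842) × 0.76), about 8.4.

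**The case against.** The strongest reply is that this is one sentence in a condensed article. Stratum-specific odds ratios and an interaction test are often reported together, and an analysis plan that is not shown may contain one. That stands as far as it goes: the lack of an interaction term here is silence, and a reader should not infer a decision against one. What remains is that the only subgroup method the article does state cannot answer the question of a differing effect.

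A reader might also infer that the investigators will compare P values across strata and announce that the intervention works in one income group and not another. The documents do not support that. No sentence says so, the hypotheses contain no subgroup claim, and results are to be reported with confidence intervals. The percentages above measure what would happen if the stratum results were read that way.

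Nor is it certain that strata will look different. If the pilot effect recurred, every equal stratum would be significant. The investigators chose to plan on 10% v 30%, so that is a fair basis, but it is the unfavourable end of the range.

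Finally, one might expect infinite odds ratios from strata with no control event. With equal strata that chance is 0.9^55 = 0.3% or 0.9^37 = 2.0% in any one stratum. Smaller, unequal strata would be sparser, but the article gives no sizes on which to base such a claim.

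**Conclusion.** The point holds in a limited form. The stated subgroup method does not test for a difference between strata. Under an identical true effect, it would show one stratum significant and another not in about 0-35% of trials for a factor with two equal strata and about 0-72% with three; the upper figures belong to the planning rates and the lower to the pilot rates. With roughly 4 to 6 control events per equal stratum, stratum odds ratios would be imprecise. All stratum figures rest on assumed numbers and sizes of strata.

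These are additional analyses. The primary comparison, with about 96% power at 220 participants under the planning rates and complete data, is not affected.

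**What to change.** For each of the four factors, fit one logistic model on all participants with arm, factor and arm-by-factor, plus the planned covariates. Report the interaction estimate with its 95% CI and P value beside the stratum-specific estimates with their CIs. State that any claim of a differing effect rests on the interaction, and label all four analyses exploratory. If the full analysis plan already provides for this, citing it is enough.

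The cost is wording and analysis code only, with no further data or participants. The downside is weaker subgroup statements: with two equal strata at 220 participants, only a ratio of odds ratios of about 8.4 would be detected with 80% power, so a non-significant interaction must not be read as evidence that the effect is the same in all groups.

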#### Secondary Outcomes

The economic evaluation will be conducted from a health care provider’s perspective with a 1-year time horizon. Microcosting methods will be used to evaluate the implementation costs of both the standard-of-care and pay-it-forward intervention groups. Specifically, we will collect cost data, including personnel time, medical supplies, equipment use, and facility expenses. Material procurement costs will be calculated using primary sources, such as invoices, while project implementation costs will be based on researchers’ self-reported data. Health care personnel’s time costs will be estimated using the local government–published wage standards. A decision tree model will be developed using TreeAge Pro 2022 software (TreeAge Software, LLC), with vaccination uptake (defined as the number of vaccinated individuals per intervention arm) serving as the effectiveness measure for the pay-it-forward intervention. The intervention will be compared against standard-of-care (participants’ self-paid PPSV-23 vaccination) to estimate incremental costs and incremental cost-effectiveness ratios. Model robustness will be assessed through 1-way sensitivity analyses and probabilistic sensitivity analysis. Influenza vaccination rates and vaccine confidence will be compared between the pay-it-forward intervention group and the standard-of-care group using logistic regression analyses, adjusted for sociodemographic information. Other secondary outcomes will be summarized using descriptive statistics and compared between the 2 arms.

Participants with missing primary outcome data (ie, vaccination status) will be reviewed. A complete case analysis will be performed if the proportion of missing primary outcome data is low (<5%). If the missing data exceed this threshold, multiple imputation methods will be applied under the assumption that the data are missing at random, to account for potential bias. Sensitivity analyses will also be conducted to assess the robustness of the findings under different assumptions about the missing data. To address missing follow-up data, we will use the last observation carried forward method or a multiple imputation method for missing values for categorical and continuous variables.

The results of all logistic regression analyses will be reported as crude odds ratios and adjusted odds ratios, along with 95% CIs. All statistical tests will be 2-sided, with a significance level of *P*<.05.

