## Methods

### Study Design and Setting

We will conduct a 2-arm, parallel randomized controlled trial among adults aged ≥60 years. Community health care centers (CHCs) will be the unit of randomization and intervention. We will recruit participants via vaccination clinics, WeChat (Tencent Technology Company Limited), and SMS text messaging. Participants will be randomly allocated to either the standard-of-care arm (self-payment for vaccinations) or the pay-it-forward arm (receiving a 150 RMB [US $20.7] subsidy for vaccination and opportunities for donation and handwritten postcards) in a 1:1 ratio through an envelope randomization mechanism, with blocks of 4 participants per group. Follow-ups are planned for the second and fourth weeks after enrollment of participants. At the end of the fourth-week follow-up, we will confirm the number of individuals vaccinated with the PPSV-23 in both groups through the vaccination information management system for the immunization program. Written informed consent will be obtained from each participant before enrollment. The CHCs are the central vaccination units for residents and have sufficient vaccine supplies and medical staff familiar with vaccination procedures, facilitating the recruitment of study participants. To ensure sample representativeness, we plan to conduct this study in Qingxiu district (high-income areas), Xixiangtang district (middle-income area), and Liangqing district (low-income area) in Nanning city, Guangxi province. All research assistants and community health care workers (CHWs) involved in this study will receive the same training. Figure 1 and Table 1 illustrate the study design and interventions.

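### The economic evaluation states a 1-year horizon but its effect measure is read once, at about 4 weeks, so the cost per additional person vaccinated may be off if later uptake differs between arms

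*Protocol article*

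**What the plan says.** Under Statistical Analysis, Secondary Outcomes, the Protocol article sets the economic evaluation from a health care provider's "perspective with a 1-year time horizon". Its decision tree has "vaccination uptake (defined as the number of vaccinated individuals per intervention arm) serving as the effectiveness measure", compared with self-paid vaccination "to estimate incremental costs and incremental cost-effectiveness ratios". No time point is attached to uptake in that section. One-way and probabilistic sensitivity analyses are planned, with no parameters named.

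The measurement time is given elsewhere. Outcome Measures defines the primary outcome as "uptake of PPSV-23 in each arm, assessed 1 month after the intervention using administrative records". Study Design and Setting says "At the end of the fourth-week follow-up, we will confirm the number of individuals vaccinated with the PPSV-23 in both groups", and also "Follow-ups are planned for the second and fourth weeks after enrollment of participants". Table 1 ends with a closeout at week 5. No later reading of PPSV-23 uptake is described.

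**The concern.** Costs and effects in an economic evaluation should cover the same window as its stated horizon. Here the horizon is 1 year and the only effect data described stop at about 4 weeks. A difference at week 4 can mix two things: people who would not otherwise have been vaccinated that year, and people vaccinated sooner than they would have been. The trial as described cannot separate them.

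This matters because cost-effectiveness is part of the stated objective, and Aims and Hypotheses says the findings should inform government decisions on vaccine subsidies. A payer wants the cost per additional person vaccinated. The Introduction gives protection of up to 5 years, so a dose taken some months later keeps most of its value.

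Some later uptake among controls is plausible. They receive the vaccine leaflet, the video and, if willing, an appointment, but must find the full price. The Strengths and Limitations section itself doubts that two surveys within a month are enough to change behaviour quickly.

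**Working it through.** **The plan's own figures.** The article states no cost-effectiveness ratio, so there is none to reproduce. The planning rates can be checked through the sample size. For 10% v 30%, 2-sided 0.05, power 90%, 1:1, with unpooled variance:

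n per arm = (0.10×0.90 + 0.30×0.70) × (1.960 + 1.282)² / 0.20² = 78.8, so 79 per arm and 158 in total, as stated. Then 158 / 0.80 = 197.5, so 198, as stated. This confirms that the projected increase is 20 percentage points.

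**Inputs.**
- Planning rates: 30% v 10% (Sample Size).
- Pilot rates: 23/26 v 3/26, that is 88% v 12% (Sample Size).
- Subsidy: 150 RMB (Abstract; Study Design and Setting).
- Uptake between week 4 and month 12: not given for either arm. All values below are assumptions.

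**Formulas.**
- Week-4 gap: D4 = p(pay-it-forward) − p(control).
- 12-month gap: D12 = D4 + late pay-it-forward uptake − late control uptake.
- Ratio = incremental cost per participant / gap. At fixed incremental cost, the 12-month ratio is D4/D12 times the week-4 ratio.
- If a share s of D4 is only brought forward, D12 = D4 × (1 − s) and the multiplier is 1/(1 − s).

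**Planning rates, D4 = 0.20.** For a scale in money, assume that the subsidy is the only incremental cost: 150 × 0.30 = 45 RMB per participant, and 45 / 0.20 = 225 RMB per additional person vaccinated.

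| Share brought forward | 12-month gap | Multiplier | Ratio (RMB) |
|---|---|---|---|
| 0% | 20 points | 1.00 | 225 |
| 10% | 18 points | 1.11 | 250 |
| 25% | 15 points | 1.33 | 300 |
| 50% | 10 points | 2.00 | 450 |

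**Other directions, same rates.**
- Late uptake of 5 points in each arm: the gap stays at 20 points. The ratio stays at 45/0.20 = 225 RMB if late doses carry no subsidy. If they do, it becomes (150 × 0.35)/0.20 = 262.5 RMB.
- Late uptake of 5 points under pay-it-forward only: the gap is 25 points. The ratio falls to 45/0.25 = 180 RMB, or 52.5/0.25 = 210 RMB if late doses are subsidised.

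**Pilot rates, D4 = 20/26 = 0.769.** The week-4 ratio is (150 × 23/26)/0.769 = 172.5 RMB. Control catch-up of 5 points gives 0.769/0.719 = 1.07 times (184.5 RMB). Catch-up of 10 points gives 0.769/0.669 = 1.15 times (198.3 RMB).

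So both the sign and the size depend on late uptake, which the described data do not observe, and the size also depends on how large the week-4 gap is.

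**The case against.** A reader might infer that the ratio is too favourable as it stands. The documents do not support that. It needs net catch-up by controls, and no later uptake is reported for either arm. Equal late uptake leaves the gap unchanged, and greater late uptake under pay-it-forward reverses the error.

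Nor can one say that only the intervention arm is pressed to act at once. Under Standard-of-Care Group, controls get the same vaccine leaflet, the video, an eligibility assessment and a scheduled appointment. What differs is the subsidy and the pay-it-forward elements, and a lower price may add uptake rather than hasten it. Nothing says that the subsidy lapses at week 4.

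A reader might also infer that the model carries the week-4 gap forward through the year. The article describes no extrapolation. Its effect is a count of people vaccinated, with no downstream illness, so the horizon does not by itself change that count. Using the week-4 count is an inference, though it is the only count described.

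Finally, model inputs are often left to a fuller plan, and sensitivity analyses are foreseen. All of this stands as a limit on the claim. It does not remove the mismatch: the article fixes both the horizon and the reading time, and they differ. A sensitivity analysis on late uptake would have no trial data behind it.

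**Conclusion.** The point holds in a conditional form. The stated horizon is 1 year, the only uptake described is at about 4 weeks, and no link between them is given. Added uptake therefore cannot be told from earlier uptake over the stated horizon. The cost per additional person vaccinated may be too favourable if controls catch up. At fixed incremental cost it is right if late uptake is equal, and too unfavourable if late uptake is greater under pay-it-forward.

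The size is unknown. Under assumed catch-up it runs from about 7% at the pilot rates (5 points) to a doubling at the planning rates (half the gap brought forward). These figures illustrate sensitivity and do not estimate a bias. The primary week-4 comparison, its analysis and the sample size are untouched. This is a low-cost improvement to a secondary result that is meant to guide policy.

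**What to change.** Keep week-4 uptake as the primary outcome. Query the same immunization registry again at 12 months after enrolment for all randomised participants, and use that uptake as the decision-tree input. Count subsidy and delivery costs over the same 12 months, and keep week-4 uptake as a sensitivity analysis. If this is not done, restate the horizon as 4 weeks and report the result as the cost per additional person vaccinated within 4 weeks.

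The query covers 220 enrolled people whose identification numbers are already recorded (Data Collection and Management) and needs no new visits. Timing allows it. Results says "Participant recruitment took place from January 2024 to September 2024", so 12 months are complete for everyone by about September 2025, before the results expected in June 2026. The costs are a small protocol and ethics note, matching cost data for late doses, and the chance that the ratio becomes less favourable. The fallback is a change of wording only, provided that costs are also confined to the 4 weeks.

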### Data Collection and Management

When participants are enrolled, the research assistants will record their enrollment time, envelope number, name, identification number, and group. Data will be collected on the professional Chinese questionnaire website Wenjuanxing [29] using self-designed questionnaires, including the baseline questionnaire (questionnaire A) and the follow-up questionnaires (questionnaires B and C). The information collected is presented in Table 2.

**Table 2 table2:** Summary of information to be collected.

Item	Questionnaire codes
Sociodemographics	A
Knowledge about PPSV-23^a^	A, B, and C
Dissemination of PPSV-23	A
Attitudes toward PPSV-23	A, B, and C
Gratitude (GQ-6^b^ scale)	A, B, and C
Willingness and reasons for receiving the PPSV-23	A
Feasibility, appropriateness, and acceptability of pay-it-forward (only pay-it-forward group)	A
Reasons for promoting or discouraging donations (only pay-it-forward group)	B and C
Incidence of adverse reactions or adverse events	B and C
Recommendation of PPSV-23 to others	B and C

^a^PPSV-23: 23-valent pneumococcal polysaccharide vaccine.

^b^GQ-6: Gratitude Questionnaire—6-item scale.

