We will collect the following information: (1) sociodemographic characteristics (eg, sex, marital status, education levels, monthly income, and employment); (2) knowledge of PPSV-23 (eg, age eligibility, reduced risk of hospitalization and death, and reduced medical costs owing to pneumonia); (3) attitudes toward PPSV-23, which will be evaluated using a standardized scale [30] to assess vaccination confidence among participants (eg, perceived safety, efficacy, and importance of the vaccine); (4) education and sensitization related to PPSV-23 (eg, recommendations from health care workers or friends); (5) tendency to show gratitude, which will be measured using the widely used Gratitude Questionnaire—6-item scale (GQ-6) [30]. (6) reasons for promoting or discouraging donations, which will be assessed among participants in the pay-it-forward group, along with the feasibility, appropriateness, and acceptability of the pay-it-forward interventions, using previously well-evaluated scales [31]. (7) incidence of adverse reactions (eg, fever, redness, swelling, pain, itching) or adverse events (eg, pneumonia, bronchitis, ear infections), which will be investigated for participants who receive vaccination; (8) reasons for declining vaccination, which will be collected from the participants who do not receive the vaccine; and (9) participants recommendations to others to receive PPSV-23.

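### Adverse reactions are collected only from vaccinated participants but are to be compared between the randomised arms; that contrast is not randomised and cannot show a safety difference or its absence

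*Protocol article*

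**What the plan says.** Three statements in the Methods of the protocol article combine.

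- **Who is asked.** Data Collection and Management, item 7, covers adverse reactions (fever, redness, swelling, pain, itching) and adverse events (pneumonia, bronchitis, ear infections), "which will be investigated for participants who receive vaccination". Table 2 in the same section lists "Incidence of adverse reactions or adverse events" under questionnaires B and C and does not repeat that restriction.
- **What is reported.** Outcome Measures makes "incidence of adverse events or reactions to vaccination" the ninth secondary outcome. No denominator is given.
- **How it is analysed.** Under Statistical Analysis, Secondary Outcomes, only the economic evaluation, influenza vaccination and vaccine confidence have their own methods. For the rest: "Other secondary outcomes will be summarized using descriptive statistics and compared between the 2 arms". Safety is not excepted. The section closes by setting a two-sided 5% level for all tests.

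The sections on the two groups describe the same vaccine in both arms. The arms differ in the subsidy, the postcards and the opportunity to donate.

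**The concern.** The group in whom reactions are recorded forms after randomisation, and membership of it is the primary outcome. A comparison of arms within that group is no longer a comparison of randomised groups. Controls who are vaccinated have paid the full price. Those vaccinated under pay-it-forward include people who would not have come without the subsidy. The two sets may differ in health, income or readiness to report symptoms.

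Nor does the comparison answer a vaccine-safety question, because the product is the same in both arms. A difference could be misread as harm from pay-it-forward. The absence of one could be misread as reassurance, although so few vaccinated controls cannot provide it. The article means its findings to inform decisions on vaccine subsidies, so either misreading could matter to its readers.

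**Working it through.** **Inputs from the article**

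- Planning rates (Sample Size): "we estimated a PPSV-23 vaccination coverage of 10% in older adults, and projected that the pay-it-forward intervention would increase this by 20"%. Read as percentage points, this is 10% v 30%.
- Pilot uptake (Sample Size): "88% (23/26) of the participants in the pay-it-forward group" and "12% (3/26) of the participants in the standard-of-care group".
- Enrolment (Results): 220, so 110 per arm if the 1:1 split is even.

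**Assumption.** The article gives no reaction rate. I take r = 10%, 20% and 30% of vaccinated people, the same in both arms.

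**Step 1: check the reading of the planning rates.** The article states 90% power and a two-sided 5% level. With the unpooled normal approximation:

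n per arm = [0.10 × 0.90 + 0.30 × 0.70] × (1.960 + 1.282)² / 0.20² = 0.30 × 10.51 / 0.04 = 78.8, so 79 per arm and 158 in total.

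158 / 0.80 = 197.5, so 198. Both stated figures are reproduced, which confirms 10% v 30%.

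**Step 2: expected numbers vaccinated.** 110 × 0.10 = 11 in standard of care, 110 × 0.30 = 33 in pay-it-forward, 44 in all.

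**Step 3: vaccinated participants as denominator.** The 95% half-width for the difference is 1.96 × √[r(1 − r)(1/11 + 1/33)]. For one group of size n it is 1.96 × √[r(1 − r)/n].

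| Assumed r | Difference, 11 v 33 | Pooled rate, n = 44 | Pay-it-forward alone, n = 33 |
|---|---|---|---|
| 10% | ±20.5 points | ±8.9 | ±10.2 |
| 20% | ±27.3 points | ±11.8 | ±13.6 |
| 30% | ±31.3 points | ±13.5 | ±15.6 |

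The normal approximation is rough with 11 controls. Exact intervals at about 20% tell the same story: 2/11 gives 2.3% to 51.8%, 7/33 gives 9.0% to 38.9%, and pooled 9/44 gives 9.8% to 35.3%.

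With equal risk in both arms, Fisher's exact test on 11 v 33 is significant in 1.8%, 2.7% and 3.2% of trials for r = 10%, 20% and 30%. Small numbers alone do not generate an excess of false positives. The defects are selection and lack of information.

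**Step 4: all randomised participants as denominator.** Incidence in an arm is uptake × r, so r cancels from the ratio: 0.30r / 0.10r = 3.0 at the planning rates, and (23/26) / (3/26) = 23/3 = 7.7 at the pilot rates. With 110 per arm and the planning rates, Fisher's test would be significant in 4.5%, 20% and 37% of trials for the three values of r. For reactions that only the vaccine can cause, such a result restates the uptake difference. Pneumonia, bronchitis and ear infection also occur in the unvaccinated, who under item 7 are not asked, so the background count is missing.

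**The case against.** The case for leaving the plan alone has several parts.

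- **The natural denominator is the vaccinated.** The wording of item 7 and of the outcome itself points that way. A reader might infer that the plan will produce a spurious harm signal against pay-it-forward. That needs an all-randomised denominator, which the article does not state. On the natural denominator, equal risk gives significant results in under 5% of trials. This stands, and the point does not rest on a false signal.
- **An all-randomised count of vaccine reactions has a meaning.** An unvaccinated person cannot have injection-site pain from PPSV-23, so not asking loses nothing there. More reactions in the arm that vaccinates more people is a real consequence of the programme. This stands too. Such a count describes uptake, however, not safety per dose, and the argument does not extend to background illnesses or non-specific fever.
- **No information is thrown away.** A reader might infer that splitting by arm wastes the reaction rate in all vaccinated participants. It does not: descriptive summaries are planned, and the pooled rate follows from the arm counts. Pooling narrows the half-width only from 10–16 points (pay-it-forward alone) to 9–14.
- **The pilot rates are an extreme.** The final sample size was not based on them, so the 7.7-fold ratio should not be treated as expected.
- **This is a condensed article.** The safety denominator and table layout may properly be left to an analysis plan, and showing events by arm is ordinary reporting. That excuses the missing denominator. It does not excuse a stated rule that compares this outcome between arms without exception.

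**Conclusion.** The point holds as a minor correction to one secondary outcome. As written, the plan compares randomised arms on an outcome recorded only in a subset that the intervention itself shapes, for a vaccine common to both arms. With about 11 v 33 vaccinated, a half-width of 20 to 31 points means the comparison can neither show a safety difference nor rule one out, and any difference found would be open to selection.

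These figures assume an even split of 220, uptake at the planning rates, every vaccinated participant answering the follow-up questionnaires, and a common reaction rate of 10% to 30%. Incomplete follow-up would reduce the numbers. Uptake nearer the pilot rates would enlarge the pay-it-forward group but leave only about 13 vaccinated controls (110 × 3/26 = 12.7). The lack of randomisation does not depend on any of these assumptions. The primary outcome and the sample size are untouched.

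**What to change.** In Secondary Outcomes, exempt the adverse reaction and event outcome from the between-arm comparison, and state instead:

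1. The denominator is all participants who receive PPSV-23, in both arms.
2. Reactions (fever, redness, swelling, pain, itching) are reported pooled over arms with a 95% CI. Counts by arm are descriptive only, without a test. If any contrast by arm is kept, it is labelled non-randomised.
3. Pneumonia, bronchitis and ear infection are reported separately as illnesses after vaccination, with a note that unvaccinated participants were not asked.

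Table 2 should carry the same restriction to vaccinated participants as item 7. The cost is a change of wording, with no new data. What is given up is an arm-specific P value that could not have been interpreted.
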